### Assessment of the outcome of treatment

The primary outcome is the efficacy of the treatment in achieving complete abortion and in terminating pregnancy. In addition, the four regimens will be compared in respect of the following outcomes: induction-to-abortion interval, when possible; the occurrence of side-effects; and women's perceptions about the treatments.

#### Efficacy

The efficacy outcome of the treatment will be classified on the basis of the subject's history and the clinical findings at pelvic US examination, as 1) complete abortion – uterus empty; 2) incomplete abortion – remnants of tissue in uterus; 3) missed abortion – intrauterine sac without heart beats; 4) failed termination of pregnancy – live pregnancy, heart beats seen in US; 5) lost to follow, outcome unknown; and 6) Other, including vacuum aspiration on woman's request or when indicated medically before outcome can be assessed.

Even if the woman aborts already after mifepristone, before administration of misoprostol, she will be given misoprostol. The initial judgment about the outcome of therapy is made at the first follow-up visit (Day 15 of the study). If the clinical findings at pelvic examination are suggestive of a continuing pregnancy, an ultrasound examination will be performed. In subjects with live pregnancy (i.e. fetal heart activity present) vacuum aspiration will be performed. In case of missed abortion the investigator may perform vacuum aspiration or continue to follow-up according to the clinical situation.

If the clinical findings at the Day 15 visit are compatible with incomplete abortion, no further action will be taken, unless judged necessary by the investigator, e.g. because of heavy vaginal bleeding or signs of pelvic infection. The final judgment on the outcome of therapy is made at the second follow-up visit on Day 43 of the study. If no emergency or elective curettage was necessary during the period up to the first menstruation, the outcome of treatment is classified as "complete abortion". The remaining cases in which curettage was done will be classified in the first analysis as "incomplete abortion". If the women discontinues the treatment and has vacuum aspiration before the outcome is known, the outcome will be regarded as "undetermined".

#### Induction-to-abortion interval

Induction- to-abortion interval is the time in hours from the start of treatment (mifepristone administration on Day 1) until the expulsion of the products of conception. According to our previous experience up to 70% of the expulsions take place in the clinic during the three-hour observation period after misoprostol administration. The time of expulsion will be recorded on the data collection forms. If expulsion does not occur at the clinic, women are asked to record the time in the daily record charts. It is understood that in very early pregnancies it may not always be possible to identify the time of expulsion.

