## Methods/design

The design of the study will be placebo-controlled, single-blind, randomized, stratified by centre and by the length of gestation: <49 days; 50–56 days; 57–63 days. A total of 3008 women with pregnancies of < 63 days from last menses (verified by ultrasound) will be recruited for the study in participating centres (188 subjects per centre; 62–64 per each strata of gestation) from among women requesting legal termination of pregnancy and who prefer medical abortion. All subjects will get 200 mg mifepristone orally, and 24 (+/- 2) hours later they will receive either: 4 placebo tablets vaginally and 2 tablets of misoprostol and 2 placebo tablets sublingually; or 4 placebo tablets vaginally and 4 tablets of 200 μg misoprostol sublingually; or 2 tablets of 200 μg misoprostol plus 2 placebo tablets vaginally and 4 placebo tablets sublingually; or 4 tablets of 200 μg misoprostol vaginally and 4 placebo tablets sublingually.

The dose and route of administration of misoprostol will be blinded to the women. Side-effects will be recorded at hourly intervals up to 3 hours after misoprostol administration. The preliminary outcome will be assessed before the woman leaves the clinic. The final outcome regarding the efficacy, side-effects since treatment and acceptability will be assessed at the follow-up visits on Day 15 and Day 42 of the study unless women are still bleeding and require a further follow-up.

This multinational trial will be carried out in 16 departments of obstetrics and gynaecology of teaching hospitals. All departments provide routine abortion services and also carry out clinical research. The trial will be conducted according to ICH-GCP guidelines and the investigators are trained to carry out research accordingly.

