### Study procedures

Before admission to the study potential subjects will undergo the following: ultrasound examination to verify the length of the pregnancy and check that the pregnancy is intrauterine. If the pregnancy is more advanced, if there is a suspicion about an abnormal pregnancy (e.g. extrauterine, molar pregnancy, etc.) the woman will not be admitted to the study; haemoglobin measurement; the blood group and Rh typing according to the routine of the centre; full medical, obstetrical and gynaecological history; full medical and gynaecological examination including pelvic examination, height, weight and blood pressure; and bacteriological examination according to the routine of the centre.

Women who fulfil the criteria for admission and who are willing and able to participate in the trial and have given their informed consent will be included in the study. Women admitted to the study will be given a diary card to record days and amount of vaginal bleeding and side-effects. The card will also give the dates of the follow-up visits. The day of start of the treatment will constitute the day of formal admission to the study (i.e. Day 1 of the study) when the length of pregnancy should not be more than 63 days. The tablet of mifepristone must be swallowed in the presence of a member of the study team who will record on the data form the date and time when the tablet was taken.

All centres will have subject numbers from 1–192. As we plan to take randomly 4 packs of tablets per centre for quality control, each centre will recruit 188 women for the study. To ensure an equal representation of women with longer duration of pregnancy (beyond 49 days) at each centre, subject numbers will be divided between each category of gestational length so that the numbers 1–64 are used for women with the duration of pregnancy up to 49 days, 65–128 for 50–56 days and 129–192 for pregnancies of 57–63 days.

After the admission visit on Day 1 all subjects will attend the clinic on three occasions during the course of the study.

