*Day 2 visit: *during this visit which 4 tablets of misoprostol are administered vaginally and 4 tablets sublingually (right after the vaginal dose the first two sublingual tablets, and when they have melted/or after 20 minutes, the additional two tablets sublingually) followed by a 3-hour clinical observation period (hourly recordings of blood pressure, pulse rate, possible side-effects and of any medications given). Both the times of tablet administration and of expulsion of products of conception, if it occurs, will be recorded on the data forms. There will be a vaginal examination at the end of the 3-hour observation period.

*Day 15 visit *is the first follow-up visit. During this visit a medical interview will take place, the diary card is reviewed and a physical and gynecological examination will take place. A blood sample is taken to measure haemoglobin and ultrasound examination is done if judged necessary from clinical findings.

*Day 43 visit *is the second follow-up visit during which the same procedures are carried out as for Day 15, but Hb measurement is not mandatory at this visit. If the woman has not had a spontaneous menstruation by the time of the second follow-up visit, she should have a further follow-up appointment at a date to be decided by the investigator, or she can provide the information by telephone if that is more convenient.

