Stratified analysis for efficacy will be conducted by gestational age (up to and including 49 days, 50–56 days and 57–63 days). Adjusted analysis by centre and for any prognostic variable showing imbalance at baseline will be performed using Mantel-Haenszel approach and/or logistic regression where appropriate. A per-protocol analysis will be performed excluding women with conditions as described in earlier sections. Efficacy will also be calculated excluding subjects with undetermined outcome. Survival analysis if appropriate will be used to compare the differences in induction-abortion intervals. Chi-square test or Fisher exact test as appropriate, will be used to compare the proportion of women with each side-effect, adjusting for multiple inferences with an appropriate technique.

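### The induction-to-abortion interval is timed from mifepristone, which is common to all arms; timing it from misoprostol would be a cheap gain in precision

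*Protocol article*

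**What the plan says.** The section on the induction-to-abortion interval fixes the time origin at mifepristone: the interval "is the time in hours from the start of treatment (mifepristone administration on Day 1) until the expulsion of the products of conception". Methods/design makes that first step common to every arm ("All subjects will get 200 mg mifepristone orally"). The four regimens separate only at the second step ("24 (+/- 2) hours later they will receive either").

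The interval section also reports from earlier experience that "up to 70% of the expulsions take place in the clinic during the three-hour observation period after misoprostol administration".

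The times needed for another origin are collected. Under Study procedures, staff are to "record on the data form the date and time when the tablet was taken" for mifepristone. For the Day 2 visit, "Both the times of tablet administration and of expulsion of products of conception, if it occurs, will be recorded on the data forms". Women who expel outside the clinic are asked to note the time in their daily record.

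Background lists the interval among the main outcomes. The section on assessment of outcome makes efficacy primary and names the interval as an additional outcome, to be compared when possible. The analysis is given under Data management: "Survival analysis if appropriate will be used to compare the differences in induction-abortion intervals".

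**The concern.** The comparison of interest is between misoprostol doses and routes. A clock started at mifepristone measures the sum of two times: the gap to misoprostol, set by appointment keeping, and the time from misoprostol to expulsion, which is the only part the regimens can affect. Variation in the first part partly scrambles the order in which women appear to expel, and rank-based survival tests work on that order.

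The gap may range over 4 hours, while most expulsions are expected within about 3 hours of misoprostol. Background gives a reason to look for a difference in speed, since uterine tonus is said to rise faster after sublingual than after vaginal administration. What is at stake is the precision with which such a difference can be seen.

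**Working it through.** The plan states no power or sample size for this outcome, so there is no figure to reproduce.

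**Inputs from the protocol article.** Gap 24 (+/- 2) h, that is 22 to 26 h; up to 70% of expulsions within 3 h of misoprostol; 3008 women in four arms; 5% allowance for loss to follow-up or undetermined outcome. Pooled arms: 3008/2 × 0.95 ≈ 1428. Single arms: 3008/4 × 0.95 ≈ 714.

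**Assumptions.** The documents do not give the actual distribution of gaps, the distribution of expulsion times or a relevant difference between regimens. The gap is taken as independent of arm and of misoprostol-to-expulsion time, and every expulsion is taken as timed.

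**Step 1: spread of the gap.**
- Uniform over 22 to 26 h: SD = 4/√12 = 1.15 h.
- Normal, with +/- 2 h as the central 95%: SD = 2/1.96 = 1.02 h.
- Upper limit, every woman at one end of the tolerance: SD = 2.0 h.

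**Step 2: variance inflation for a uniform gap**, 1 + SD(gap)²/SD(misoprostol to expulsion)².
- Exponential, 70% by 3 h: SD = 3/1.204 = 2.49 h; 1 + 1.333/6.21 = 1.21.
- Exponential, 60% by 3 h: SD 3.27 h; inflation 1.12.
- Exponential, 50% by 3 h: SD 4.33 h; inflation 1.07.
- Lognormal, median 2.3 h and 70% by 3 h: SD 1.41 h; inflation 1.67.

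The fixed 24 h offset has no effect on rank tests or on differences in means. Only the variation matters.

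**Step 3: log-rank test, simulated.** Weibull times with 70% expelled by 3 h, 3000 runs per setting, two-sided 5%. Efficiency is the squared ratio of mean z (mifepristone origin over misoprostol origin). The two normal gaps are truncated at +/- 2 h. Results for 1428 per pooled arm and hazard ratio 1.12:

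| Weibull shape | Power from misoprostol | Uniform gap: efficiency, power | Normal gap, SD 1 h: efficiency, power | Normal gap, SD 0.5 h: efficiency, power |
|---|---|---|---|---|
| 1 | 85% | 0.84, 80% | 0.90, 81% | 0.96, 84% |
| 1.5 | 85% | 0.71, 71% | 0.81, 77% | 0.92, 81% |
| 2 | 86% | 0.57, 62% | 0.70, 71% | 0.87, 81% |

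Check of the starting power: ln(1.12) × √(2856/4) = 3.03, and Φ(3.03 − 1.96) = 86%. Other runs of these settings gave efficiencies from about 0.54 to 0.90 for the two wide gaps and 0.86 to 0.97 for SD 0.5 h.

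**Step 4: dependence on effect size and pooling.** A hazard ratio of 1.12 here is a difference in medians of about 8 to 11 minutes; 1.20 is about 12 to 17 minutes.
- Pooled arms (1428), hazard ratio 1.20: power is above 99% from misoprostol and about 95-99% with the two wide gaps.
- Single arms (714), hazard ratio 1.20: 93% from misoprostol, 74-89% with the two wide gaps.
- Single arms, hazard ratio 1.12: about 56-58% from misoprostol, 37-53% with the two wide gaps.

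**Step 5: type I error.** With no true difference, exponential times and 680 per arm (1500 runs), log-rank rejection was 5.5% from misoprostol and 6.1% from mifepristone for a uniform gap, and 4.9% and 5.1% with all gaps at the limits. The simulation error is about 0.6 points, so both origins are consistent with 5%.

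**The case against.** The strongest defence is that the stated origin is a coherent choice. Start of treatment covers the whole regimen, and the interval from mifepristone is the woman's total time to abortion. The Efficacy section foresees women who abort before misoprostol, and this origin keeps them on a positive time scale without a special rule. That stands, and it is a reason to keep the interval as a description. It does not make it the better scale for comparing misoprostol regimens.

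The role of the outcome is also limited. It is not primary, no non-inferiority conclusion depends on it, and all the times are recorded, so the other interval can be derived later. That stands too and keeps the severity low. Naming the compared interval beforehand still avoids choosing the origin after the data are seen.

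Two stronger readings are tempting, and the documents do not support them.
- A reader might infer that the noise is as large as the window in which the arms can differ. That sets a permitted range (4 h) against a 3 h window. The tolerance is not an observed spread, and even when filled it gives an SD of only about 1.0 to 1.15 h.
- A reader might infer that the definition could hide a clinically important difference in speed. The protocol states no relevant difference. In pooled comparisons the loss is visible mainly for median differences of around ten minutes with widely spread gaps.

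**Conclusion.** The point holds as a minor, cheap improvement. The interval starts at a step common to all arms, so variation in the gap to misoprostol lowers the precision of the dose and route comparisons. Women are randomized and blinded to dose and route, so this variation should be the same in every arm. The effect is attenuation, without bias or inflated type I error.

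The direction does not depend on the assumptions, but the size does. Efficiency near 55% needs both tightly clustered expulsion times and gaps spread evenly over the tolerance. With good timekeeping (SD 0.5 h) the loss of power at a hazard ratio of 1.12 in the pooled comparison is about 2 to 5 points. The loss matters most for small differences and for the unpooled comparisons that Data management foresees for efficacy if dose and route interact.

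**What to change.** In the section on the induction-to-abortion interval, define the interval compared between regimens as the time from misoprostol administration on Day 2 to expulsion. One clock time suffices: the start of Day 2 tablet administration, which is comparable across arms because every woman takes both vaginal and sublingual tablets.

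Count expulsions before misoprostol as time zero and report their number by arm. They precede any difference between the regimens, so little information is lost. Keep the interval from mifepristone as a descriptive summary of total time to abortion.

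The cost is a changed definition plus one rule for the early expulsions. No new data are needed, and no dose, schedule or clinical procedure changes.

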#### Incidence of side-effects

Signs and symptoms will be recorded at admission, and women will keep daily records of any complaints and medication taken, for the duration of the whole trial and report them at each visit. Data on signs and symptoms will be collected prior to misoprostol administration and immediately after administration as well as at one-hour intervals up to three hours. In addition, the intensity of side effects is recorded indicating whether side-effects were mild, moderate or severe. However, the pain is recorded using the scale from 0–10, in which 0 means no pain and 10 is the worst possible pain the subject can imagine.

We classify the signs and symptoms that women may have during the trial as follows: Pregnancy-related symptoms: such as nausea, vomiting, breast-tenderness, fatigue, dizziness, headache and fainting; Drug-related side-effects, such as diarrhoea, fever and rash; and side-effects related to the abortion process, such as lower abdominal pain and bleeding.

#### Women's perceptions

Women's perceptions on the treatments are assessed at the first follow-up visit using slightly modified versions of the questionnaires from our previous trials.

An individual subject's participation in the study is discontinued if she wants to withdraw her participation or is lost to follow-up. Side-effects such as nausea, vomiting, uterine pain, etc. that may occur in some women during the course of the induced abortion do not constitute a reason for discontinuation and will be treated symptomatically where necessary.

An independent Data Monitoring Committee (DMC) will be appointed to monitor the safety of the study. Its members will discuss the results of interim analyses, will assess whether the magnitude of the difference in the outcomes and side-effects is clinically relevant and/or whether it is associated with the treatment and will give recommendations to the trial Steering Committee regarding stopping the trial prematurely. The ultimate decision about the study discontinuation will be the responsibility of the trial co-ordinator, who without delay will make the information about such a decision available to the participating centres. If any investigator is worried about any symptoms related to the treatment (s)he has to inform the Programme immediately.

The decision whether or not to discontinue a lower dose regimen, because of low efficacy will be based on its comparison with the regimen of 200 mg mifepristone followed by 800 μg misoprostol vaginally 24 hours later. Two interim analyses will be conducted, respectively, when data for 700 subjects are available for analysis in the electronic data file and when data for 1300 subjects are available, or at any point when DMC requests for it. The significance level at the final analysis will be adjusted using Haybittle-Peto rule.

Pre-admission tests and haemoglobin measurement (Days 1 and 15) will be carried out by methods routinely employed at each centre. Ultrasound examinations will be done to verify the length of the pregnancy before admission and, if judged necessary from clinical findings, any time during the study.

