### Data management

Participating centres will be requested to record the data on paper data collection forms, enter them and send them electronically on a weekly basis to Geneva, using a Web-based system [14]. Recruitment and data quality will be monitored by the Programme's Statistics and Informatics Services Team using this system.

Data will be analyzed centrally in Geneva. Descriptive statistics will be calculated for all baseline characteristics for all subjects randomized, by treatment group, to describe characteristics of the population and to assess comparability of the groups. The overall summary statistics for women who complete the trial will be compared with those for the subjects lost to follow-up.

All subjects randomized having known outcome will be included in the main efficacy analysis in their randomized groups. If attempts fail to locate and contact a woman lost to follow-up, and her outcome of treatment is not known, then that woman will be excluded from the efficacy analysis. If she has information on side effects, she will be included in the safety analysis. Baseline characteristics of women lost to follow-up will be compared with those completing the study and between groups, to explore the possibility of bias due to these differences.

Crude rates for each outcome will be calculated in each arm and exact confidence intervals based on the binomial distribution calculated as described in Armitage and Berry [15]. If the interaction of misoprostol route by misoprostol dose is significant at 5% level, comparisons will be made between routes for each dose and between doses for each route. If the interaction is not significant at 5%, two comparisons will be made, between routes for the two doses combined, and between doses for the two routes combined. For these comparisons, relative risks (RR) of failure to achieve a complete abortion and failure to terminate pregnancy and the two-sided 95% CIs will be calculated by standard methods, as well as risk differences and two-sided 95% CIs. The latter will be used to test the non-inferiority hypotheses (at 2.5% level of significance) for achieving complete abortion.

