#### Number of subjects and statistical power

To establish the non-inferiority (one-sided equivalence) of the 400 μg misoprostol (sublingual or vaginal) regimen compared to the 800 μg with respect to efficacy, we require the upper limit of the one-sided 95% confidence interval (or the two-sided 95% confidence interval) for a difference in complete abortion rates (that of 800 μg minus that of 400 μg) to be within a margin of equivalence of 3%. It is estimated that if the abortion rates in the two regimens are both equal to 95%, about 680 subjects will be required in each group to demonstrate non-inferiority with a power of 80%, i.e. a total of about 2720 subjects. To allow for a 5% of women lost to follow-up or with undetermined outcomes, then about 720 women will have to be recruited per group, a total of about 2880. If 15 centres participate in the study, 192 subjects will be needed in each centre. However, to ensure recruitment in one year time, we plan to include one additional centre, 16 centres in all. Since we plan to take four packs per centre for quality control, the actual number of women recruited per centre will be 188. These calculations allow for the presence of an interaction between misoprostol dose and its route of administration.

For the choice of the non-inferiority margin, a clinical criterion was used, not a statistical one. This is based on the fact that there are not placebo-controlled trials available and the efficacy of placebo would be close to zero. We set the margin at 3% based on clinical assessment that this difference is not relevant.

It is estimated that the trial will require 12 to 14 months for data collection at each centre and between 6 and 12 months of centralized data analysis in Geneva.

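### The threshold for the primary non-inferiority claim is given in three forms: adjusted for interim looks (no value stated), one-sided 2.5%, and one-sided 5% or 2.5%

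*Protocol article*

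**What the plan says.** The final threshold appears in four places in the protocol article.

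- **Interim-analysis text (under Women's perceptions):** "The significance level at the final analysis will be adjusted using Haybittle-Peto rule". No interim limit and no adjusted final level are given. The looks are described as "Two interim analyses will be conducted, respectively, when data for 700 subjects are available for analysis" and "when data for 1300 subjects are available, or at any point when DMC requests for it". One efficacy decision is described specifically: "The decision whether or not to discontinue a lower dose regimen, because of low efficacy will be based on its comparison" with the 800 μg vaginal regimen. The same text lets the monitoring committee judge differences in outcomes and recommend stopping the trial early.
- **Abstract (Methods) and Data management:** two-sided 95% intervals for the risk differences are calculated, and "The latter will be used to test the non-inferiority hypotheses (at 2.5% level of significance) for achieving complete abortion". Neither place mentions an adjustment.
- **Number of subjects and statistical power:** the criterion is "we require the upper limit of the one-sided 95% confidence interval (or the two-sided 95% confidence interval") for the difference, 800 μg minus 400 μg, lying within 3%. The calculation assumes 95% complete abortion on both doses, 80% power and about 680 women per group.

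**The concern.** The upper confidence limit, set against 3%, decides the primary claim. A one-sided 95% interval tests at 5%, a two-sided 95% interval at one-sided 2.5%, and a Haybittle-Peto adjustment at a little under whichever of these is taken as the overall level. The document endorses all three and does not say which governs. A result with an upper limit near 3% could be called non-inferior under one section and not under another, and nothing in the text prevents that choice from being made once the data are known. The stated 80% power also depends on which threshold was meant.

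**Working it through.** **Inputs from the protocol.** Complete abortion 95% in both groups, margin 3 points, power 80%, 680 evaluable per group, 5% loss, 3008 women in four groups (752 each), looks at 700 and 1300 women.

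**Assumptions.** The interim limit is not stated, so I varied it from Z = 3 to Z = 3.29 (two-sided p = 0.001). Information is taken as proportional to women recruited, with exactly two looks. Looks requested ad hoc by the monitoring committee are not modelled.

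**Step 1: which level gives 680?** Unpooled formula: n = (z₁₋α + z₀.₈₀)² × 2 × 0.95 × 0.05 / 0.03².

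- One-sided 5%: (1.645 + 0.842)² × 0.095 / 0.0009 = 653.
- One-sided 2.5%: (1.960 + 0.842)² × 0.095 / 0.0009 = 829.

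Farrington-Manning formula, with the null variance taken from rates restricted to differ by 3 points (about 96.1% and 93.1%, summed variance 0.1016): n = [(z₁₋α √0.1016 + 0.842 √0.095) / 0.03]².

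- One-sided 5%: 683.
- One-sided 2.5%: 869.

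The stated 680 is reproduced at one-sided 5% (683) and by neither formula at 2.5%. The loss allowance is consistent: 680 / 0.95 = 716, or about 720.

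**Step 2: 5% against 2.5%.** At 680 per group, SE = √(0.095 / 680) = 1.182 points. Power = Φ(3 / SE − z). At 714 evaluable per group (752 × 0.95), SE = 1.153 points.

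| | One-sided 5% | One-sided 2.5% |
|---|---|---|
| Half-width at 680 | 1.645 × 1.182 = 1.94 points | 1.960 × 1.182 = 2.32 points |
| Largest observed difference that passes | 3 − 1.94 = 1.06 points | 3 − 2.32 = 0.68 points |
| Power at 680 | 81.4% | 71.8% |
| Power at 714 | 83.0% | 73.9% |

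At 680 per group, an observed deficit between 0.68 and 1.06 points passes one rule and fails the other. If the doses are truly equal, that happens with probability 81.4 − 71.8 = 9.6 points.

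**Step 3: adjusted against 2.5%.** Information fractions are 700/3008 = 0.233, 1300/3008 = 0.432 and 1. The three test statistics are jointly normal with correlations √(tᵢ/tⱼ). If success could be claimed at any look, the overall error and the final critical value that restores 0.025 are:

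| Interim limit | Overall error with final 1.960 | Final critical value | Final one-sided level | Matching two-sided interval |
|---|---|---|---|---|
| Z = 3 | 0.0263 | 1.984 | 0.0236 | 95.27% |
| Z = 3.29 | 0.0254 | 1.968 | 0.0246 | 95.09% |

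The half-width at 680 per group moves from 2.317 to between 2.326 and 2.345 points, that is by 0.01 to 0.03. Power at 680 falls from 71.8% to between 71.0% and 71.6%; at 714 it falls from 73.9% to between 73.1% and 73.7%.

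If the looks can only remove a regimen for low efficacy, they add no route to a false claim of non-inferiority, and the final test at 1.960 keeps its 2.5% level.

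**The case against.** The strongest reply is that 2.5% can be read as the overall level, with the interim text merely saying how the looks are handled. Haybittle-Peto leaves the final level nearly unchanged, and an article that condenses a full protocol may leave the exact value to that document or to the analysis plan. For the adjusted-versus-2.5% gap this largely stands: the difference is under 1 point of power, and a missing decimal alone would not merit comment. It does not answer the sample-size section, which states two different levels outright.

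Three stronger readings are tempting, and the document does not support them.

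- A reader might infer that the sample-size section also fixes 2.5%. It does not: it accepts "the upper limit of the one-sided 95% confidence interval (or the two-sided 95% confidence interval"), and its 680 matches 5%.
- A reader might infer that the interim adjustment is misplaced because the looks serve only to drop a low dose for low efficacy. The monitoring text is wider than that. The committee may recommend stopping early on outcome differences, so an early positive claim is not clearly excluded.
- A reader might infer that the trial as a whole is underpowered. The 72% to 74% applies to comparing doses within one route, which the protocol makes if the interaction is significant at 5%. If the routes are pooled (2 × 680 = 1360 per dose), the same formula gives 97.4% at one-sided 5% and 94.8% at 2.5%.

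**Conclusion.** The point holds: the primary decision rule appears in three forms that need to be reconciled. The material part is 5% against 2.5%. It moves the confidence limit by 0.37 points (2.317 − 1.944) at 680 per group and changes per-route power from 81% to 72%, against the stated 80%. The Haybittle-Peto part is a real inconsistency of wording but a small one: a final level of 0.0236 to 0.0246, a shift in the limit of 0.01 to 0.03 points, and less than 1 point of power.

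The power figures rest on 95% in both groups and the unpooled normal approximation. The Haybittle-Peto range rests on the assumed interim limits and exactly two looks. Because further looks on request are allowed, neither end of that range can be presented as the trial's adjusted level.

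**What to change.** Use one final rule in the abstract, the interim-analysis text, Data management, and Number of subjects and statistical power.

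1. In the sample-size section, delete the one-sided 95% option so that the two-sided 95% interval (one-sided 2.5%) governs, in line with the abstract and Data management.
2. Restate the power there for the per-route comparison at that level: about 72% at 680 per group and about 74% at 714 evaluable per group (unpooled).
3. In the interim-analysis text, say whether a look can lead to an early claim of non-inferiority. If it cannot, say so and keep the final level at 2.5%. If it can, state the sponsor's interim limit and the final level and interval that follow from it, allowing for unscheduled looks, and carry these into the other sections.

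The interim limit is the sponsor's to supply; this review does not propose one. The cost is a few sentences in the protocol and a corrected power statement, before any unblinded comparison. No added data collection is needed to state the rule. Restoring 80% per-route power at 2.5% would take 829 (unpooled) to 869 (Farrington-Manning) evaluable women per group; whether to seek that is a separate decision.
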